## Introduction

1.

Coronary heart disease (CHD) is one of the leading causes of death worldwide (Nowbar et al., 2019). Psychological distress such as significant symptoms of depression and anxiety are common in CHD patients (30–40%) (Reid et al., 2013) and commonly occur both immediate and longer periods of time after an acute cardiac event (Palacios et al., 2016). In an observational study from Norway, we reported prevalence rates of depression and anxiety of 14.7 and 21.1%, respectively, as assessed by the Hospital Anxiety and Depression Scale (HADS), mean 16.7 months after a CHD event (Frøjd et al., 2022b).

Patients with CHD have increased mortality risk with depression or anxiety alone being associated with up to two-fold increased risk of cardiovascular events and mortality (van Melle et al., 2004; Watkins et al., 2013). Depression and anxiety commonly co-occur and in those with both conditions, the prognosis is particularly poor with three-times increased risk of mortality (Watkins et al., 2013). Furthermore, associations between depression and anxiety have been reported for higher rates of cardiovascular risk factors, such as smoking and low physical activity, lower treatment adherence and higher levels of markers of immune function (Munkhaugen et al., 2018). The latter risk factor, more specific C-Reactive Protein (CRP), is an independent risk factor for recurrent cardiovascular events in CHD patients (Ridker et al., 2017). In addition, anxiety and depression symptoms are linked to poorer quality of life, higher rates of hospital admissions and work retention (Holdgaard et al., 2023).

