### Eligibility criteria

2.4.

Patients will be asked to participate in the study if they meet the following inclusion criteria:

Previously hospitalized with myocardial infarction and/or angiography-verified atherosclerosis.A score of ≥8 on the HADS-anxiety and/or depression subscales.Age ≥ 18 to ≤65 years.Ability to understand and speak the Norwegian language.Signed informed consent.

Patients will be excluded if they meet any of the following criteria:

Current or past neurological illness, traumatic brain injury.Current alcohol and/or substance dependency disorders.Psychotic disorders, bipolar disorders, developmental disorders or learning disabilities.Cognitive impairment which precludes informed consent/ability to participate.Acute suicidality.Life-expectancy less than 12 months.Concurrent psychological intervention for emotional distress.Antidepressant or anxiolytic medication initiated or changed during the past 8 weeks.

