### Recruitment and allocation

2.5.

Consecutive patients hospitalized with a CHD event during the past years (2011–2022) at the department of cardiology at Drammen hospital or Vestfold hospital will be assessed for eligibility. All potentially eligible patients will be selected from hospital discharge lists by searching chronologically after last admission for the index event during the past years (2011–2022) prior to study inclusion. A specially-trained research cardiac nurse will screen the hospital records. All eligible patients (*N*⁓1,500) will be mailed a comprehensive self-report questionnaire as part of a follow up study addressing psychological distress. The responses will be screened by a research nurse and those who score ≥ 8 for HADS-A and/or HADS-D will be mailed information about the ATT-CHD study and consent to be contacted for further information and evaluation if they return a signed informed consent form together with a recent score ≥ 8 on either of the HADS subscales. Those who meet our eligibility criteria will be offered a face-to-face evaluation, and information about the study if eligible. Those who consent to participate will undergo diagnostic interviews as well as self-report assessments before being randomized and allocated to either ATT immediately or wait-list control. Randomization will be performed by a study statistician blinded to the results of the evaluations. An online software tool is used for randomization with a block- and list-size of 8–12 persons (Sealed Envelope Ltd, 2022. Create a blocked randomization list^1^). The randomization program will be kept in a secured, logged hard disk. Before randomization, baseline data will be collected (Table 1).

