### Outcomes

2.11.

Primary outcomes are: changes in HADS-anxiety and HADS-depression scores from pre-treatment to post-treatment and 6 months follow-up between treatment arms. Changes in the proportion of patients scoring below 8 on HADS-anxiety and HADS-depression, respectively, from pre-treatment to post-treatment and 6-months follow-up between treatment arms.

Secondary outcomes are changes in psychiatric disorders, rumination, worry, type D-personality, insomnia, quality of life and metacognitions scores, as well as CRP levels, from pre-treatment to post-treatment and 6-months follow-up between treatment arms. In addition, qualitative data will be collected and evaluated.

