#### Primary outcome

2.12.1.

Hospital Anxiety and Depression Scale: The HADS (Zigmond and Snaith, 1983) is a 14 item self-report scale measuring anxiety (7 items) and depression (7 item). Responders rate distress based on the past 7 days. Each item is scored using a 4-point Likert-scale (from 0 to 3). A score ≥ 8 on either of the subscales indicates a significant level of anxiety and/or depression, respectively (Bjelland et al., 2002). Scores from 0 to 7 are categorized as normal, from 8 to 10 as mild, 11–14 moderate and 15 to 21 severe. The HADS has been employed in several CHD studies with good psychometric properties (Haddad et al., 2013).

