### Sample size and power calculation

2.13.

Statistical power calculation was based on the primary outcome of HADS with subscale outcomes of HADS-depression and HADS-anxiety. A conservative anxiety/depression effect size from previous studies of individual and group ATT for depression was used (0.67). This effect size is similar to what has been reported in a meta-analytic study of CBT and other psychological treatments (0.67) (Cuijpers et al., 2010). Thus, based on previous research, we expected a difference between the two conditions (ATT and WLC) amounting to an effect size of approximately 0.67. Allowing for 15–20% drop out in accordance with previous studies, we aim for a final sample size of 32 in each group, i.e., 64 in total. This yields a statistical power above 90% using a two-sided significance test (*p* < 0.05).

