#### Quantitative analysis

2.14.1.

A repeated measures linear mixed-model will be used to estimate treatment effects for the combined sample, with HADS-A and HADS-D scores as outcomes, from pre-treatment, post-treatment and 6 months follow-up. Controlled effect sizes will be calculated in the following way: post treatment for immediate ATT minus post waiting list divided by the pooled standard deviation. Both ITT and per protocol analyses will be reported.

The primary reported analyses will be carried out as an intention-to-treat with all randomized participants. The analysis is supplemented with per-protocol analyses defined by participation in ≥4 of the 6 group-based sessions. Missing information on other co-variates will be permitted if there is <20% missing data for the co-variate in question. Age, gender, HADS-D and HADS-A scores will be entered in the models as covariates if baseline differences are observed.

An estimate of treatment effect size will be derived by comparing the wait-list control and intervention group on levels of symptoms of anxiety and depression (HADS), rumination (RRS), worry (PSWQ), insomnia (BIS), metacognitive beliefs (MCQ-30, PBRS, NBRS) and inflammation (CRP) at baseline, end of treatment and 6 months follow-up. False discovery rate will be applied for multiple testing (Benjamini and Hochberg, 1995).

Analyses will be undertaken using Stata SE vs. 18.0 (StataCorp, 2023) and/or R (R Core Team, 2021) and conducted by a statistician who will remain blind to group allocation throughout. A detailed statistical analyze plan (SAP) will be prepared and published prior to analyses taking place.

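### The per-subscale HADS responder outcome counts patients already below 8 on that subscale at entry, which dilutes the between-arm difference

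*Protocol article*

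**What the plan says.** Eligibility (section 2.4) asks for "A score of ≥8 on the HADS-anxiety and/or depression subscales", so one raised subscale suffices. Recruitment (section 2.5) applies the same either-subscale rule: "those who score ≥ 8 for HADS-A and/or HADS-D will be mailed information about the ATT-CHD study".

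Under primary outcomes (section 2.11), after the continuous changes in the two subscale scores, the article lists "Changes in the proportion of patients scoring below 8 on HADS-anxiety and HADS-depression, respectively". The sentence goes on to measure this from before treatment to its end and to the 6-month visit, and to set the arms against each other. That matters: this is a change, compared between arms, judged on each subscale separately.

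Section 2.12.1 gives the meaning of the threshold: "Scores from 0 to 7 are categorized as normal". Section 2.14.1 sets the analysis population: "The primary reported analyses will be carried out as an intention-to-treat with all randomized participants". Nothing in the article limits the responder outcome to patients who scored 8 or more on the subscale concerned at baseline.

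**The concern.** The entry rule and the responder rule use the same cut-off but different logic: entry needs either subscale, while response is judged on each. A patient who enters on anxiety alone sits in the normal range of HADS-D from the start. On the HADS-D criterion that patient can only stay put or get worse. The same holds for HADS-A in a patient who enters on depression alone.

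Each such patient takes up a place in the denominator without being able to contribute a favourable change. The between-arm difference therefore shrinks in proportion to their share, and in a trial of 32 per arm there is little power to spare. A null result on this outcome would be hard to read: it could mean that ATT does not bring symptomatic patients below the threshold, or that few patients had anything to recover from on that subscale. The stated primary objective (section 1.1) concerns patients with significant symptoms, and the outcome as written does not isolate them.

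**Working it through.** **The plan's own figures.** The article gives no response rate and no power for the proportion below 8. Its only power figure (above 90%, section 2.13) is for a standardised mean difference, "amounting to an effect size of approximately 0.67". A plain two-sample calculation with 32 per arm and two-sided 0.05 gives about 76% for that. The gap is a separate matter and nothing below rests on it.

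**Share already below 8 at entry.** The Introduction says of the group's own coronary cohort: "we reported prevalence rates of depression and anxiety of 14.7 and 21.1%, respectively". The overlap is not given. Assume that entrants resemble that cohort, and let U be the share with either subscale raised.

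- Full overlap: U = 0.211. No overlap: U = 0.147 + 0.211 = 0.358.
- Below 8 on HADS-D: 1 − 0.147/U, from 1 − 0.147/0.211 = 30.3% to 1 − 0.147/0.358 = 58.9%. Of 64 patients, that is 19 to 38.
- Below 8 on HADS-A: 1 − 0.211/U, from 0% to 1 − 0.211/0.358 = 41.1%. Of 64, that is 0 to 26.
- Between the bounds, assume a bivariate normal model with latent correlation 0.4 to 0.7. U is then 29.6% to 26.3%, the share below 8 on HADS-D is 50% to 44%, and on HADS-A 29% to 20%.

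**Dilution on HADS-D.** Let s be the share already below 8. If these patients behave alike in both arms, the difference seen in all patients is (1 − s) times the difference among cases. For an assumed 30-point difference among cases:

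- s = 30.3%: 0.697 × 30 = 20.9 points, with 0.697 × 32 = 22 cases per arm.
- s = 58.9%: 0.411 × 30 = 12.3 points, with 13 cases per arm.
- Latent correlation 0.4 to 0.7: 15 to 17 points, with 16 to 18 cases per arm.

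**Power, for illustration.** Assume that 20% (wait-list) and 50% (ATT) of HADS-D cases fall below 8, and ignore dropout. Power = Φ(Δ/√((v0 + v1)/n) − 1.96). For a proportion, v = p(1 − p). For a change score, v = u + w − (u − w)², where u is the share newly below 8 and w the share newly at or above it.

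Example, change version, s = 30.3%: u = 0.139 and 0.348, Δ = 0.209, standard error √((0.120 + 0.227)/32) = 0.104, power Φ(2.01 − 1.96) = 52%.

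| Analysis | s = 30.3% | s = 58.9% |
|---|---|---|
| All patients, post-treatment proportion | 40% | 20% |
| All patients, change, no non-case crosses 8 | 52% | 30% |
| All patients, change, 10% of non-cases rise to 8 or more in both arms | 43% | 20% |
| Baseline cases only (22 or 13 per arm) | 60% | 40% |

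If all 32 per arm were cases, the same formula gives 76%. Pooling the variance under the null lowers these somewhat (baseline cases only 56% and 36%, post-treatment proportion 39% and 20%, all cases 72%).

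**The case against.** The strongest reply is that the outcome is a change in proportion. A patient below 8 at both visits contributes zero, so the baseline level is subtracted. That stands. A reader might infer that recovery rates are inflated in both arms; this would be true of raw post-treatment rates, but the article does not define the outcome that way. The same subtraction weakens any argument from chance imbalance in which subscale was raised, although the room to improve could still differ between arms.

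Second, the change in the share with raised scores among all randomised patients is a legitimate quantity: it keeps the full intention-to-treat set and counts new cases. That also stands. Dilution pulls towards no difference, and nothing here suggests a false benefit.

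Third, a reader might call this a co-primary endpoint on which the trial's conclusion turns. The article does not use that term. Its abstract names changes in HADS as the primary outcome, and both the power calculation and the mixed model concern the continuous scores. The proportion is nevertheless listed among the primary outcomes.

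Fourth, a reader might infer that many patients already meet the criterion on both subscales. The article supports this for HADS-D only, since the HADS-A bound includes zero. The upper bounds need no overlap at all, whereas the Introduction says that the two conditions commonly occur together.

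Fifth, the promised analysis plan could set the denominator. It could, but the article already fixes the outcome in all patients, and a plan that follows it would inherit the problem.

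**Conclusion.** The point holds as a matter of design. Sections 2.4, 2.5, 2.11 and 2.14.1 together put into each subscale's responder analysis patients who cannot improve on it. The change wording cures the baseline level, not the dilution.

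The size is conditional. At least about 30% already below 8 on HADS-D assumes that entrants resemble the cohort in the Introduction, although entrants are 65 or younger and must return a recent qualifying score. The 12–21 point range follows from an assumed 30-point difference among cases; 15–17 points also assumes the latent correlations above. The power figures rest on the assumed 20% and 50%.

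They also show a limit. Against the change version, restricting to baseline cases gains about 8 to 10 percentage points of power if no non-case crosses the threshold, and more if some do. It does not restore what a full set of 32 cases per arm would give. Much of the gain is in interpretation. This is a worthwhile, cheap correction to one listed primary outcome, and it leaves the continuous HADS comparison as it is.

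**What to change.** Before analysis, restate the responder outcome in two parts:

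- **Subscale recovery.** The proportion below 8 on HADS-A among randomised patients with baseline HADS-A of 8 or more, and likewise for HADS-D.
- **Full intention-to-treat responder outcome.** Below 8 on both subscales, in all randomised patients. Under the entry rule nobody meets this at the qualifying screen. Some may by the pre-treatment visit if scores drift, so the baseline count should be reported.

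Compare both between arms at the end of the randomised wait-list phase, since wait-list patients go on to receive ATT before the 6-month visit. Adjust for baseline HADS scores, for example by logistic regression with arm and both scores.

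The cost is a change of wording and one derived variable from data already collected. The subscale rates will rest on smaller denominators, possibly about 13 per arm for HADS-D before the 15–20% dropout that the article allows for. The composite merges two outcomes that the protocol reports separately, which is why the subscale rates should stay alongside it.

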### Measures

2.12.

#### Primary outcome

2.12.1.

Hospital Anxiety and Depression Scale: The HADS (Zigmond and Snaith, 1983) is a 14 item self-report scale measuring anxiety (7 items) and depression (7 item). Responders rate distress based on the past 7 days. Each item is scored using a 4-point Likert-scale (from 0 to 3). A score ≥ 8 on either of the subscales indicates a significant level of anxiety and/or depression, respectively (Bjelland et al., 2002). Scores from 0 to 7 are categorized as normal, from 8 to 10 as mild, 11–14 moderate and 15 to 21 severe. The HADS has been employed in several CHD studies with good psychometric properties (Haddad et al., 2013).

#### Secondary outcomes

2.12.2.

##### Diagnostic interviews

2.12.2.1.

A structured interview for DSM-5 Disorders (SCID-5-CV) (First et al., 2016), and a structured clinical interview for DSM-V axis II disorders (SCID-5- PD) (First et al., 2015) will be used.

##### Ruminative Response Scale (RRS)

2.12.2.2.

The RRS (Nolen-Hoeksema and Morrow, 1991) is a 22-item scale assessing tendency to ruminate in response to depressed mood. The RRS contains items tapping the meaning of rumination (e.g., “I write down what I am thinking about and analyze it”), the feelings related to depressed mood (e.g., “I think about how sad I feel”), symptoms of depression (e.g., “I think about how hard it is to concentrate”), and consequences and causes of depressed mood (e.g., “I think I will not be able to do my job if I do not snap out of this”). Responses are required on a 4-point rating scale ranging from 1 (*almost never*) to 4 (*almost always*). The reported Cronbach alpha for the RRS is 0.92 (Nolen-Hoeksema and Morrow, 1991). We will apply the total score.

##### Penn state worry questionnaire (PSWQ)

2.12.2.3.

The PSWQ (Meyer et al., 1990) is a 16-item self-report questionnaire designed to measure the trait worry. Examples of items of the PSWQ are “I worry all the time” and “My worries overwhelm me.” Responses are rated on a five-point Likert scale ranging from 1 (“not at all typical of me”) to 5 (“very typical of me”). The PSWQ has good psychometric properties (Startup and Erickson, 2006). The reported Crohnbach alpha for the PSWQ is 0.93 (van Rijsoort et al., 1999).

##### Type D personality questionnaire

2.12.2.4.

The type D personality questionnaire (DS14) (Denollet, 2005) is a self-report scale consisting of two subscales, negative affectivity and social inhibition. Each subscale consists of seven items, amounting to a total of 14 items and rated on a five-point Likert scale (0–4). A person is identified as having type D personality if the score on both scales is ≥10.

##### Bergen Insomnia Scale (BIS)

2.12.2.5.

The BIS (Pallesen et al., 2008) is a six-item questionnaire based on the criteria for the clinical diagnosis of insomnia described in the *Diagnostic and Statistical Manual of Mental Disorders*, fourth version (DSM-IV-TR). The first four items inquire about difficulties with sleep initiation, maintenance of sleep, awakenings in the morning, and nonrestorative sleep; items five and six assess daytime impairment and satisfaction with sleep. A 30 min cutoff value is used for the first three items. All items are scored as number of days per week (0–7), yielding a continuous sum score from 0 to 42 (BIS sum score), increasing with severity of insomnia symptoms. The BIS can also be used as a diagnostic tool (insomnia vs. no insomnia). Three days or more on items one, two, three, or four combined with 3 days or more on item five or six indicate a diagnosis of insomnia. The BIS has adequate psychometric properties, and there are normative Norwegian data for comparison (Pallesen et al., 2008). In the present study, the 4-week test–retest reliability of the BIS was 0.92 (Peersen et al., 2017). The BIS was included in this study because BIS-insomnia has been associated with poor prognosis in CHD patients (Frøjd et al., 2022a) and our previous feasibility study demonstrated ATT to reduce insomnia (Dammen et al., 2022).

##### Short Form−12 (SF-12)

2.12.2.6.

The SF-12 (Ware et al., 1996) is a 12-item self-report questionnaire that rates on a five-point Likert scale. It assesses health outcomes from a patients’ perspective and measures health related quality of life (HRQoL). It is designed so that a higher score indicates a better health state. The questionnaire has items measuring physical functioning (two items), role-physical (two items), bodily pain (one item), general health (one item), vitality (one item), social functioning (one item), role-emotional (two items) and mental health (two items).

##### Metacognitions Questionnaire−30 (MCQ-30)

2.12.2.7.

The MCQ-30 (Wells and Cartwright-Hatton, 2004) is a 30-item self-report scale. It measures five different domains of metacognition (cognitive confidence, positive beliefs about worry, cognitive self-consciousness, negative beliefs about uncontrollability and danger, need to control thoughts). Each item is measured on a 4-point Likert scale (ranging from 1 to 4), and based on agreeableness to the specific item.

##### Negative Beliefs about Rumination Scale (NBRS)

2.12.2.8.

The NBRS (Papageorgiou et al., 2001) is a 13-item scale assessing negative metacognitive beliefs about rumination. Example items include “Ruminating about my problems is uncontrollable” and “People will reject me if I ruminate.” Respondents are required to indicate the extent to which they agree with each of the items on a 4-point rating scale ranging from 1 (*do not agree*) to 4 (*agree very much*). The reported Cronbach alpha for the NBRS is 0.82 (Papageorgiou et al., 2001).

##### Positive Beliefs about Rumination Scale (PBRS)

2.12.2.9.

The PBRS (Papageorgiou and Wells, 2001) is a 9-item scale that assesses positive metacognitive beliefs about the perceived benefits and advantages of rumination. Example items include “I need to ruminate about my problems to find answers to my depression” and “Ruminating about the past helps me to prevent future mistakes and failures.” Respondents are required to indicate the extent to which they agree with each of the items on a 4-point rating scale ranging from 1 (*do not agree*) to 4 (*agree very much*). The reported Cronbach alpha for the PBRS is 0.89 (Papageorgiou and Wells, 2001).

#### Sociodemographic and clinical data

2.12.3.

Other data from hospital medical records and self-report questionnaires collected at baseline will include gender, age, information about CHD index event and treatment, time elapsed between the index event and randomization, somatic comorbidity and risk factors (diabetes and hypertension), marital status (single, married or cohabiting, divorced, separated or widowed), education (in years), age at onset of depressive or anxiety episodes, length of depressive/anxiety illness, duration of current anxiety/depressive episode, number of previous depressive episodes, previous therapy for mental disorders and use of alcohol and medication (including sedatives/hypnotics).

